#### 6.5.1.10 Protocol visit #9: Off study assessment: 6 months (+/- 14 days) after the first dose of IFN- $\gamma$

- Clinical outcome monitoring: Any reaction or symptoms related to the IFN- $\gamma$  or DLI will be assessed, specifically focusing on active grade II-IV GVHD or de novo grade III-IV, or progressive chronic GVHD. Other clinical outcomes, including the latest disease status, will be recorded.
- STR chimerism of peripheral blood (CD3 and myeloid)
- Optional bone marrow aspirates (no biopsy) will be performed for morphology, flow cytometry, and research sample (10ml). Cytogenetics/molecular testing only needed if clinically indicated to follow MRD if clinically indicated.
- Research sample collection: 10ml of bone marrow (green top heparin tube) if collected, 30 mL of peripheral blood (10 mL green top heparin tube x 3 tubes) will be collected.

### 6.5.2 Protocol Visits for Cohort 2

#### 6.5.2.1 Pre-treatment bone marrow aspirates for research (within two weeks before IFN- $\gamma$ administration)

- **Bone marrow aspirates** (no biopsy) will be performed for morphology, flow cytometry, and research sample (10mL) if the bone marrow research sample is not collected within two weeks before the first dose of IFN- $\gamma$ . The bone marrow aspirate for research can be performed concurrently with protocol visit #1, the first dose of IFN- $\gamma$ .

#### 6.5.2.2 Protocol visit #1: Stage 1, the first dose of IFN- $\gamma$

- Pre-treatment assessment (bone marrow aspirates, vital signs, and clinical assessment) as described in 6.3.1 will be performed before IFN- $\gamma$  administration.
- **Bone marrow aspirates** (no biopsy) will be performed for morphology, flow cytometry, and research sample (10mL) if the bone marrow research sample is not collected within two weeks before the first dose of IFN- $\gamma$ .
- Research sample collection: A bone marrow aspirate with a goal of 10 mL collected (in 10ml green top heparin tube x 1) and 30 mL of peripheral blood (10 mL green top heparin tube x 3 tubes) will be obtained as a baseline sample before IFN- $\gamma$  administration.
- First dose of IFN- $\gamma$  will be administered after the safety assessment.
- As described in 6.3.1., the patient will receive the training for self-injection of IFN- $\gamma$
- Safety monitoring: Subjects will be assessed for an acute reaction to the IFN- $\gamma$  or complication of biospecimen collection. Subjects will stay in the clinic for at least 1 hour after IFN- $\gamma$  administration and be assessed by a physician, physician assistant, advanced practice nurse or nurse prior to discharge from the clinic.

6.5.2.3 Protocol visit #2: Stage 1, minimally 48 hours (up to one week) after the first dose of IFN- $\gamma$ : Safety and biological assessment of IFN- $\gamma$ , bone marrow aspiration for research

- Clinical safety monitoring: Any reaction or symptoms related to the prior doses of IFN- $\gamma$  and will be assessed specifically focusing on active grade II-IV GVHD or de novo grade III-IV, or progressive chronic GVHD
- **Bone marrow aspirates** (no biopsy) will be performed for morphology, flow cytometry, and research sample (10mL).
- Research sample collection: 10mL of bone marrow (10ml green top heparin tube), 30 mL of peripheral blood (10 mL green top heparin tube x 3 tubes) will be collected.
- The subsequent doses of IFN- $\gamma$  will be administered after the safety assessment.

6.5.2.4 Protocol visit #3: End of stage 1 and pre-treatment evaluation for stage 2 (donor lymphocyte infusion), Day +7 (-3 days to +5 days) after the first dose of IFN- $\gamma$ : Safety assessment of IFN- $\gamma$

- Clinical safety monitoring: Any reaction or symptoms related to the prior doses of IFN- $\gamma$  and will be assessed specifically focusing on active grade II-IV GVHD or de novo grade III-IV, or progressive chronic GVHD
- Laboratory monitoring: CBC with differential, chemistry panel (Na, K, Cl, CO2, creatinine, glucose, urea nitrogen, phosphorus, magnesium, albumin, calcium, LDH, uric acid), hepatic (alkaline phosphatase, ALT, AST, and total bilirubin) panel
- The subsequent doses of IFN- $\gamma$  will be administered after the safety assessment.
- If DLI is available, the first dose of DLI will be infused within two weeks from this visit.

6.5.2.5 Protocol visit #4: Stage 2 first safety assessment, 21 days (+/- 5 days) after the first dose of IFN- $\gamma$ , or 14 days (+/- 5 days) after the first dose of DLI.

- Clinical safety monitoring: Any reaction or symptoms related to the IFN- $\gamma$  or DLI will be assessed, specifically focusing on active grade II-IV GVHD or de novo grade III-IV, or progressive chronic GVHD
- Laboratory monitoring: CBC with differential, chemistry panel (Na, K, Cl, CO2, creatinine, glucose, urea nitrogen, phosphorus, magnesium, albumin, calcium, LDH, uric acid), hepatic (alkaline phosphatase, ALT, AST, and total bilirubin) panel
- The subsequent frequency IFN- $\gamma$  will be reduced to once-weekly dosing for four more weeks.

6.5.2.6 Protocol visit #5: Stage 2 follow up safety assessment, 35 days (+/- 5 days) after the first dose of IFN- $\gamma$ , or 28 days (+/- 5 days) after the first dose of DLI

- Clinical safety monitoring: Any reaction or symptoms related to the IFN- $\gamma$  or DLI will be assessed, specifically focusing on active grade II-IV GVHD or de novo grade III-IV, or progressive chronic GVHD
- Laboratory monitoring: CBC with differential, chemistry panel (Na, K, Cl, CO2, creatinine, glucose, urea nitrogen, phosphorus, magnesium, albumin, calcium, LDH, uric acid), hepatic (alkaline phosphatase, ALT, AST, and total bilirubin) panel
- STR chimerism of bone marrow (if collected) and peripheral blood (whole blood, or CD3 and myeloid)
- Research sample collection: 30 mL of peripheral blood (10 mL green top heparin tube x

3 tubes) will be collected.

- Optional bone marrow aspirates (no biopsy) will be performed for morphology, flow cytometry, and research sample (10ml) if clinically indicated. Cytogenetics/molecular testing only needed if clinically indicated to follow MRD if clinically indicated.
- If the second or third dose of DLI is available, the DLI will be infused at minimal 4 weeks of interval in the absence of active grade II-IV GVHD or de novo grade III-IV, or progressive chronic GVHD requiring new treatment or increased doses of current treatment per treating physician's determination.
- There is an optional bone marrow aspirate if clinically indicated before the second or the third DLI per the treating physician, and research sample (10mL in green top heparin tube) will be collected.

6.5.2.7 Protocol visit #6: Stage 2 follow up safety assessment, 56 days (+/- 7 days) after the first dose of IFN- $\gamma$  (= approximately 49 days +/- 7 days after the first DLI or 21 days +/- 7 days after the second DLI)

- Clinical safety monitoring: Any reaction or symptoms related to the IFN- $\gamma$  or DLI will be assessed, specifically focusing on active grade II-IV GVHD or de novo grade III-IV, or progressive chronic GVHD
- Laboratory monitoring: CBC with differential, chemistry panel (Na, K, Cl, CO2, creatinine, glucose, urea nitrogen, phosphorus, magnesium, albumin, calcium, LDH, uric acid), hepatic (alkaline phosphatase, ALT, AST, and total bilirubin) panel
- Research sample collection: 30 mL of peripheral blood (10 mL green top heparin tube x 3 tubes) will be collected.
- Optional bone marrow aspirates (no biopsy) will be performed for morphology, flow cytometry, and research sample (10ml) if clinically indicated. Cytogenetics/molecular testing only needed if clinically indicated to follow MRD if clinically indicated.
- If the third dose of DLI is available, the DLI will be infused at minimal 4 weeks of interval in the absence of active grade II-IV GVHD or de novo grade III-IV, or progressive chronic GVHD requiring new treatment or increased doses of current treatment per treating physician's determination.
- There is an optional bone marrow aspirate if clinically indicated before the third DLI per the treating physician, and research sample (10mL in green top heparin tube) will be collected.

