Cohort 2: As we confirmed the safety of IFN- $\gamma$  monotherapy in the first cohort, we will evaluate a second cohort wherein we will shorten IFN- $\gamma$  monotherapy (stage 1) to 1 week before DLI. In stage 1, we will assess the safety a fixed-dose of IFN- $\gamma$  (100mcg subcutaneously three times per week) for one week. The bone marrow biopsies will be performed before and no earlier than 48 hours to 1 week after the first dose of IFN- $\gamma$  to assess malignant blasts for an IFN- $\gamma$  response. In stage 2, subjects who have tolerated IFN- $\gamma$  will receive DLI in a dose-escalating manner. IFN- $\gamma$  will be continued three times a week for seven weeks after the first dose of DLI, followed by once-weekly IFN- $\gamma$  for four weeks. The patients will be off treatment after a 12 week-course of IFN- $\gamma$  with a repeat bone marrow biopsy at this point. The clinical outcomes will be monitored at six months after the first dose of IFN- $\gamma$  and then the subjects will be off study. Figure 2 summarizes the study design for cohort 2.

Sample size: Our goal is to have at least three patients receive at least one dose of DLI. For example, if the first three patients all complete stage 1 and stage 2, this initial pilot study would be completed with three patients. We estimate enrolling six total patients, but not likely more than nine, as some patients may not be able to complete the study due to the development of rapid disease progression or unavailability of DLI. Based on the nature of the transplant populations at our centers, we estimate accrual will be completed within six months.

For cohort 2, we aim to enroll six patients receiving IFN- $\gamma$  and at least one dose of DLI.

[figure not shown]

**Figure 1. Study Design of Cohort 1:** The figure outlines the scheme of how to administer IFN- $\gamma$  and subsequent donor lymphocyte infusions after enrollment. Biospecimens will also be collected, as shown. BM: bone marrow aspirates, DLI: donor lymphocyte infusion, IFN- $\gamma$ : interferon-gamma, PBMC: peripheral blood mononuclear cells

[figure not shown]

**Figure 2. Study Design of Cohort 2:** The figure outlines the scheme of how to administer IFN- $\gamma$  and subsequent donor lymphocyte infusions after enrollment. Biospecimens will also be collected, as shown. BM: bone marrow aspirates, DLI: donor lymphocyte infusion, IFN- $\gamma$ : interferon-gamma, PBMC: peripheral blood mononuclear cells

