**Figure 4. The dose adjustment plan for IFN- $\gamma$  for cohort 1.**

- Schedule of IFN- $\gamma$  and dose adjustment for cohort 2 (Figure 5)
- 1) The initial dose of IFN- $\gamma$
- a. The first dose of IFN- $\gamma$  100 mcg will be administered on day 0 in the clinic.
  - b. The subject will continue self-injection of 100mcg, three times a week for two weeks (e.g., Monday, Wednesday, Friday or Tuesday, Thursday, Saturday)

- 2) 48 hours after the initial dose of IFN- $\gamma$  (up to 1 week)
  - a. Bone marrow aspirate (no biopsy) will be performed for morphology, flow cytometry, and a research sample. (Cytogenetics/molecular testing only needed if clinically indicated to follow MRD.)
- 3) One week after the initial dose of IFN- $\gamma$  (window: - 3 days to + 7 days)
  - a. Subjects tolerating 100 mcg three times a week can proceed to DLI if eligible.
  - b. If the subject is not tolerating a given dose, it can be decreased to 100mcg two times a week for one week (+/- 5 days). If tolerated, the patient would then be eligible to proceed to the DLI phase.
  - c. If 100 mcg two times per week is not tolerated, IFN- $\gamma$  will be discontinued, and the subject will be withdrawn from further on-study treatment. The subject may still proceed to DLI off study.

[figure not shown]

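### Cohort 2 is defined by one week of IFN-gamma before DLI, but its visit windows allow the first DLI on days 4 to 26 (or 28) and allow the first post-DLI safety visit to fall before DLI

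*Protocol*

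**What the plan says.** The Synopsis (Cohort 2) says that the second cohort will shorten IFN-gamma "monotherapy (stage 1) to 1 week before DLI".

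The step from stage 1 to DLI is then given in several places:

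- Section 6.3.2, cohort 2 schedule, item 3, places it one week after the first dose, with "window: - 3 days to + 7 days".
- Section 6.5.2.4 (visit #3, end of stage 1) gives "Day +7 (-3 days to +5 days) after the first dose of IFN"-gamma. Appendix D has the same -3/+5 window and marks DLI in the visit #3 column.
- Section 6.5.2.4 also states: "If DLI is available, the first dose of DLI will be infused within two weeks from this visit". IFN-gamma goes on meanwhile: subsequent doses "will be administered after the safety assessment". Cohort 1's end-of-stage-1 visit (6.5.1.5) carries the same two-week allowance.

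Section 6.5.2.5 describes visit #4 as "Stage 2 first safety assessment, 21 days (+/- 5 days) after the first dose of IFN"-gamma, or alternatively 14 +/-5 days after the first DLI. Section 6.5.2.6 does the same for visit #5 (day 35, or DLI + 28). Appendix D lists only days 21 and 35. In cohort 1 the corresponding visits (6.5.1.6 and 6.5.1.7) are timed from DLI, and the alternative timing is reserved for subjects who get no DLI.

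**The concern.** The length of IFN-gamma exposure before DLI is the feature that sets cohort 2 apart from cohort 1. If sites can follow the text exactly and still give DLI two or three weeks late, the cohort label no longer describes the exposure.

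The second issue is the timing of the safety data. Adverse events with concurrent DLI are a primary endpoint (1.1.3.2, 8.1.1), and section 2.2 names GVHD as the main safety concern. A visit meant to look at patients about two weeks after DLI should not be satisfiable before the infusion.

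The analysis is descriptive, so no error rate is affected. The numbers are small, however: the Synopsis aims for six cohort 2 patients with DLI, and 8.2.1 for at least three and up to six. One patient with a late DLI would be between one sixth and one third of the cohort.

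**Working it through.** **1. The plan's own figure.** Subtracting the paired anchors gives the assumed day of first DLI: visit #4, 21 - 14 = 7; visit #5, 35 - 28 = 7; visit #6 (6.5.2.7), 56 - 49 = 7. The taper rule in 6.4.2.2 (8 weeks from IFN-gamma, about 7 from DLI) gives 8 - 7 = 1 week. The nominal one-week lead-in is reproduced.

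**2. Range that the windows allow.** Earliest DLI = start of the end-of-stage-1 window. Latest DLI = end of that window + 14 days.

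- Cohort 2, 6.5.2.4: visit #3 on days 7 - 3 = 4 to 7 + 5 = 12; DLI on days 4 to 26.
- Cohort 2, 6.3.2: days 4 to 7 + 7 = 14; DLI on days 4 to 28.
- Cohort 1, 6.5.1.5: visit #4 on days 28 - 5 = 23 to 28 + 5 = 33; DLI on days 23 to 47.
- Overlap of the cohorts: days 23 to 26 (or 23 to 28).

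**3. IFN-gamma doses before DLI.** Three doses a week were counted from each possible starting weekday, assuming that this frequency continues up to DLI.

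| First DLI on day | Doses before DLI |
|---|---|
| 4 | 2 |
| 7 (intended) | 3 |
| 21 | 9 |
| 23 (cohort 1 earliest) | 10 |
| 26 | 11 or 12 |
| 28 (cohort 1 nominal) | 12 |

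**4. Visit #4 against DLI.** Timed from IFN-gamma, visit #4 falls on days 21 - 5 = 16 to 21 + 5 = 26. The most by which it can precede DLI is the latest DLI day minus 16.

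| Visit #3 on day | Latest DLI | Visit #4 can precede DLI by up to |
|---|---|---|
| 4 | 18 | 2 days |
| 7 | 21 | 5 days |
| 12 | 26 | 10 days |
| 14 (6.3.2 only) | 28 | 12 days |

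**5. How far the two anchors diverge.** Timed from a DLI on day 26, visit #4 would fall on days 26 + 9 = 35 to 26 + 19 = 45, which shares no day with 16 to 26. In general the two visit #4 windows share a day only if DLI day + 9 is at most 26, that is, DLI by day 17. With DLI on day 26, visit #5 on day 35 is 35 - 26 = 9 days after DLI instead of 28, and visit #6 on day 56 is 30 days after it instead of about 49.

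**The case against.** **Overlap only at the edge.** It needs a late visit #3 and nearly the full two weeks. With visit #3 on day 7, the latest DLI is day 21, before cohort 1's earliest day 23. Setting 12 doses against 12 compares cohort 2's extreme with cohort 1's nominal value; like for like it is day 7 against 28, or day 26 against 47. This stands, and it limits the overlap. It does not remove the conflict with the one-week lead-in, since day 21 is three times the stated week and needs only the written allowance.

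**A sensible reader would use the DLI anchor.** Visit #4 belongs to stage 2, the DLI stage, and timing it from DLI always puts it after the infusion. Appendix D's fixed days settle nothing, because Appendix C also lists fixed days for cohort 1 visits that the text ties to DLI. This is fair, and it makes the point an ambiguity rather than an instruction to assess early. But cohort 1's text says who may use the alternative, and cohort 2's does not.

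**Stronger readings that the documents do not support.**

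- A reader might infer that GVHD surveillance after DLI can be met with no post-DLI observation. Visit #5 timed from IFN-gamma starts on day 30, after even a day-28 DLI. Visits #6 to #9 follow, each assessing GVHD, and adverse events are collected to at least visit #8 for patients who complete IFN-gamma (9.5).
- A reader might infer that cohort 2 cannot answer its own question. No between-cohort test is planned, and patients treated near day 7 would still inform it. The windows only fail to ensure the intended exposure.
- A reader might infer that the visit #2 marrow can follow DLI, since its window runs to day 7 and DLI may start on day 4. Section 6.3.2, the visit order in 6.5.2 and Appendix D all put that marrow in stage 1, before visit #3, and DLI is allowed only from visit #3.

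**Conclusion.** The inconsistency is real and should be fixed. The stated lead-in is one week, while the text permits the first DLI on days 4 to 26, or to day 28 with the 6.3.2 window, and the two windows for the same step disagree. Pre-DLI exposure can range from 2 to about 12 doses against an intended 3. The overlap with cohort 1 is confined to days 23 to 26 (or 28).

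Because the governing anchor is unstated, visit #4 can precede a day-26 DLI by up to 10 days, and visit #5 on day 35 can come 9 days after it. The effect is displaced early post-DLI assessment in a small descriptive cohort, not absent safety follow-up.

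These figures rest on four assumptions: the two-week allowance is used as written; Appendix D's DLI mark at visit #3 does not override it; dosing stays at three times a week until DLI; and neither cohort uses its provisions for a reduced injection frequency. The cohort 2 reduced-frequency branch in 6.3.2 would lengthen the time before DLI further.

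**What to change.** - Reconcile the Synopsis (Cohort 2), 6.3.2, 6.5.2.4 and Appendix D on the visit #3 window and the two-week DLI allowance, against the stated one-week lead-in. The limit is for the sponsor to choose.
- Reconcile the two timings of visits #4 and #5 in 6.5.2.5, 6.5.2.6 and Appendix D, so that a scheduled post-DLI safety assessment cannot be met before DLI has been given.
- Tabulate cohort 2 safety by actual interval from first IFN-gamma to first DLI, as well as by cohort.

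The cost is protocol wording, an edit to Appendix D and one further descriptive table, with no added visits or procedures. If the sponsor narrows the allowance, some patients whose donor cells arrive late would fall outside it. The interval table would still show their data in a cohort of this size.

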#### 6.4.2.2 For the subjects for whom donor leukocytes are available (cohort 2)

- After the first dose of DLI, the same dose of IFN- $\gamma$  as used pre-DLI for that patient will be continued three times a week for four weeks. If the subject develops intolerance to IFN- $\gamma$  during this period, we will reduce the frequency of IFN- $\gamma$  to once weekly.
- A minimum of four weeks after the first dose of DLI, the subject will receive the second DLI, in the absence of active grade II-IV GVHD or de novo grade III-IV, or progressive chronic GVHD requiring new systemic treatment or increased doses of current systemic treatment per treating physician's determination. IFN- $\gamma$  will be continued at the same dose three times weekly. There is an optional bone marrow aspirate if clinically indicated prior to the second DLI per the treating physician, and a research sample can be collected at that time.
- 8 weeks after the first dose of IFN- $\gamma$  (or approximately 7 weeks after the first dose of DLI), the frequency of IFN- $\gamma$  will be tapered to once weekly, continued until the next DLI.
- A minimum of 4 weeks after the second DLI, the subject will receive the third dose of DLI, in the absence of active grade II-IV GVHD or de novo grade III-IV, or progressive chronic GVHD defined by a requirement for new systemic treatment or increased doses of current systemic treatment. IFN- $\gamma$  will be continued at the same dose once weekly for three more weeks. There is an optional bone marrow aspirate if clinically indicated before the third DLI, and a research sample may also be collected at that time.
- IFN- $\gamma$  will be continued once weekly until four weeks of the last dose of DLI or 12 weeks after the first dose of IFN- $\gamma$  whichever occurs later. If the subject develops intolerance to IFN- $\gamma$  during this period, we will discontinue IFN- $\gamma$
- At the end IFN- $\gamma$  treatment, the bone marrow aspirate is required ideally within seven days after the last dose of IFN- $\gamma$

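### Cohort 2 visit #4 cuts IFN-γ to once weekly two weeks after the first DLI, contradicting the synopsis and the week-8 taper in section 6.4.2.2

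*Protocol*

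**What the plan says.** **Visit text, cohort 2.** Section 6.5.2.5 places visit #4 21 days after the first IFN-γ dose, or 14 days after the first DLI. It states that the frequency of IFN-γ "will be reduced to once-weekly dosing for four more weeks". Visit #6 (6.5.2.7, day 56) gives no instruction on frequency.

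**Synopsis, cohort 2.** After one week of monotherapy, IFN-γ "will be continued three times a week for seven weeks after the first dose of DLI", then once weekly for four weeks. The synopsis adds: "The patients will be off treatment after a 12 week-course of" IFN-γ.

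**Section 6.4.2.2, cohort 2.**
- First bullet: the same dose "as used pre-DLI for that patient will be continued three times a week for four weeks" after the first DLI.
- Second bullet: at the second DLI, a minimum of four weeks after the first, IFN-γ "will be continued at the same dose three times weekly".
- Third bullet: taper to once weekly 8 weeks after the first IFN-γ dose, put at about 7 weeks after the first DLI.
- End rule: IFN-γ "will be continued once weekly until four weeks of the last dose of DLI or 12 weeks after the first dose of" IFN-γ, whichever is later.

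**DLI timing.** Visit #3 (6.5.2.4, nominal day 7) says: "If DLI is available, the first dose of DLI will be infused within two weeks from this visit".

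**Cohort 1.** Visit #5 (6.5.1.6), 14 days after the first DLI or two weeks after the end of stage 1 for non-DLI subjects, carries the same sentence as cohort 2 visit #4. The synopsis and 6.4.2.1 give DLI subjects four weeks of three-times-weekly dosing after DLI. Section 6.4.2.3 gives subjects without DLI two more weeks, then weekly dosing to week 12.

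**The concern.** The cohort 2 text gives different answers to one question: when does IFN-γ drop to once weekly after the first DLI? Visit #4 says two weeks, while the synopsis and the taper bullet of 6.4.2.2 say about seven. The visit #4 cut is unconditional, so it cannot be the reduction for intolerance that 6.4.2.2 also provides.

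The second primary safety endpoint (1.1.3.2 and 8.1.1) is adverse events of IFN-γ with concurrent DLI, so the amount of IFN-γ given after DLI is the exposure being described. Cohort 2 plans for three to six DLI recipients (8.2.1 and synopsis). One or two patients dosed on a different schedule would blur the descriptive tables of adverse events, GVHD and blast burden that are meant to inform a phase II trial. Patients inject at home and two centers take part, so the instruction given at a visit bears on what is injected.

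**Working it through.** **Inputs.** Visit days come from 6.5.2 and Appendix D for cohort 2, and from 6.5.1 and Appendix C for cohort 1. Assumptions: full tolerance, three injections per full week, treatment ending at week 12.

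**Formula.** Doses = 3 × (weeks at three times weekly) + 1 × (weeks at once weekly).

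**The plan's own schedule, cohort 2, DLI on day 7.** The synopsis gives 1 + 7 + 4 = 12 weeks, which matches its 12-week course. The 6.4.2.2 taper gives 8 + 4 = 12 weeks. The two agree.

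| Reading | Total doses | Doses after DLI |
|---|---|---|
| Synopsis | 1×3 + 7×3 + 4×1 = 28 | 7×3 + 4 = 25 |
| 6.4.2.2, week-8 taper | 8×3 + 4×1 = 28 | 7×3 + 4 = 25 |
| Visit #4, then weekly to week 12 | 3×3 + 9×1 = 18 | 2×3 + 9 = 15 |

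Reduction in total doses: 1 − 18/28 = 36%. After DLI: 1 − 15/25 = 40%.

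**A later end of treatment.** With DLI on days 7, 35 and 63 (minimum four-week gaps), the end rule runs to day 63 + 28 = 91, or week 13. Each reading gains one weekly dose and the difference stays at 10.

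**A later first DLI.** Visit #3 allows DLI up to day 7 + 14 = 21. Visit #4 timed from DLI then falls on day 35 and gives 5×3 + 7 = 22 doses against 28 under the week-8 taper (21% fewer). In this case the synopsis and 6.4.2.2 also part company: seven weeks after DLI is week 3 + 7 = 10, not week 8.

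**The first bullet of 6.4.2.2.** If the second DLI is given at about four weeks, the first three bullets run in sequence: three times weekly to the second DLI, three times weekly after it, taper at week 8. If the second DLI is absent or delayed, weeks 4 to 7 after the first DLI are left in conflict. If the four-week bullet alone controlled, with weekly dosing assumed thereafter, the total would be (1 + 4)×3 + 7 = 22. Visit #4 would still be lower, by 1 − 18/22 = 18%.

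**Cohort 1, DLI on day 28.** Synopsis and 6.4.2.1: 4×3 + 4×3 + 4 = 28 doses, 16 of them after DLI. Visit #5 at day 42, then weekly to week 12: 4×3 + 2×3 + 6 = 24 (14% fewer), 12 of them after DLI. For non-DLI subjects, 6.4.2.3 gives (4 + 2)×3 + 6 = 24, so the timing of the step-down agrees with visit #5. The four weeks stated there would end at week 6 + 4 = 10, however, while 6.4.2.3 runs to week 12.

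**The case against.** Section 6.4.2 is the dosing section, and a careful site would follow it over a line in a visit list. The safety analysis is descriptive (8.1.1.1). Exposure already varies by design, through reductions for intolerance, physician-determined DLI doses, one to three infusions and discretionary stopping. Patients keep an injection diary (6.3.2), so the doses actually taken can be recovered.

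Much of this stands and limits the weight of the point. It does not remove the contradiction. Visit #4 is the only cohort 2 visit that instructs a change in frequency, and visit #6, on the intended taper day, is silent. A site working from the visit list would step down at the wrong time.

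Some stronger readings are tempting but not supported:

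- **That visit #4 ends treatment four weeks later.** The end rule of 6.4.2.2 sets week 12 as the earliest end, visit #7 places end of therapy at 12 weeks, and Appendix D marks IFN-γ at visit #6 (day 56).
- **That a DLI on day 21 would coincide with the cut.** This needs visit #4 to be timed from the first IFN-γ dose, which would put a post-DLI safety visit on the day of the DLI. The alternative timing of 14 days after DLI is the sensible one.
- **That the four-week bullet is a contradiction for every patient.** It conflicts with the taper only when the second DLI is absent or delayed.
- **That a DLI-driven course beyond week 12 is itself an error.** The end rule in 6.4.2.2 allows it.

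**Conclusion.** The contradiction is real and should be corrected. In cohort 2, visit #4 gives 18 doses against 28 under the synopsis and the week-8 taper, and 15 against 25 after DLI. These figures assume DLI on day 7, full tolerance and a week-12 end. If DLI falls on day 21, the gap narrows to 22 against 28. No reading of the synopsis or 6.4.2.2 supports a step-down two weeks after DLI.

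The visit #4 sentence is identical to that of cohort 1 visit #5, so carry-over is the likely cause, but the document does not prove it. The cohort 1 conflict affects DLI subjects only (24 versus 28 doses). It probably has little prospective effect, since the synopsis describes monotherapy safety in that cohort as already confirmed.

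A reader might infer that patients were under-dosed or that the biological endpoint is compromised. The document shows neither. Nothing indicates that a site followed the visit text, and the primary marker comparison uses marrow taken 48 hours to one week after the first dose, before visit #4.

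**What to change.** 1. Delete the once-weekly sentence from cohort 2 visit #4. Place the step-down at visit #6 (day 56), with a reference to 6.4.2.2.
2. Change the first bullet of 6.4.2.2 to three times weekly until 8 weeks after the first IFN-γ dose, whether or not a second DLI has been given.
3. Anchor the cohort 2 taper in the synopsis to the same week-8 point, so that a later DLI does not create a second taper date. Keep the 6.4.2.2 end rule (four weeks after the last DLI or week 12, whichever is later).
4. Limit the cohort 1 visit #5 sentence to non-DLI subjects, with weekly dosing to week 12 as in 6.4.2.3.
5. If any patient was dosed by the visit text, report the doses received after DLI, taken from the injection diary, beside the safety tables.

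Cost: a short clarifying amendment (one sentence deleted, one added, three changed) and a memo to the sites. It needs no extra patients, visits or procedures.
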